### Recruitment {15}

Study launching meetings and press releases will be organized at each recruitment centre. Information (mailings, flyers, and posters) will be distributed to partners of the different centres, including support groups, social services, and medico-social and associative structures. Clinicians of the participating centres will screen their active files for eligible participants in order to inform parents and children about the RESIST RCT protocol. The study will be presented to patients and their parents with appropriate information letters during a routine visit or via e-mail using patients’ contact information. If the patients/parents show interest in the study, a pre-inclusion visit is scheduled.

## Methods

### Assignment of interventions (for controlled trials)

#### Allocation

##### Sequence generation {16a}

The randomization will be done with Ennov-Clinical software (CS-random module). The randomization will be centralized, available online, and stratified by minimization based on centre and on two age classes (6–11 and 12–15 years) and medication status (according to major classes of psychotropic), balanced with a 1:1:1 ratio. Each subject (i.e., here duo or trio of child and parents), who meets the eligibility criteria and signed informed consent, will be randomly assigned to one of the three study groups by the study investigator.

##### Concealment mechanism {16b}

The allocation sequence will be implemented after completion and signature of the baseline visit on the e-CRF.

##### Implementation {16c}

The randomization will be done by the clinical research centre of Montpellier University Hospital after confirmation of patients’ and parents’ participation.

Participants will be enrolled by the centre of Montpellier during the pre-inclusion. This visit can be done following a routine appointment in the centres or after a previous e-mail contact. The site investigator or clinician will first give the family information about the research and provide patients with information and consent forms. An investigator from Montpellier will join the families by phone or videocall to answer further questions and check inclusion and exclusion criteria.

Informed consent and assent will be obtained from parents, children, and adolescents before any trial-specific procedures are performed. Participants will be advised that research is entirely voluntary.

The centre will aim to obtain consent from both parents, although the participation for one parent only is possible. In the latter situation, the centre will document it.

#### Blinding

##### {17a}

After the signature of informed consent and verification of inclusion and exclusion criteria, the investigators involved in the assessments will be blinded to the type of program received by the parents. This aspect will be monitored throughout the study and parents will be instructed before every assessment to avoid disclosing the type of therapy received. Investigators will be different from the therapists involved in NRV and PMT.

##### {17b}

There is no procedure for revealing a participant’s allocated intervention during the trial, because it is not a protocol targeting a pharmacological treatment. Therefore, it did not seem necessary to provide circumstances for and an unblinding protocol.

## Methods

### Data collection, management, and analysis

#### Data collection methods {18a}

Each assessment will be collected for each participant in accordance with the study data collection form by the investigator(s) or the clinical study technician(s) in charge of the study.

#### Socio-demographic assessments

The socio-demographic and early development questionnaire used for clinical and research purposes at the coordinating site at the CHU of Montpellier will be used.

### Questionnaires and Scales

#### Primary outcomes

##### Affective reactivity index (ARI)

The parent-rated ARI [29, 30] is a 6‐item scale that both clinicians and parent answer. The ARI asks about symptoms of irritability and includes a 7 item assessing impairment due to irritability. The scale shows excellent internal consistencies with Cronbach's alphas 0.89 (parent‐reported) and 0.90 (clinician-reported). The ARI has been translated into French by Maire [36].

The clinician-rated ARI [26] has been chosen as the main efficacy variable of the study to rate all available information while keeping main outcome variable (group allocation) blinded. The CL-ARI contains verbal prompts and examples to lead the administrator through the items. A total of 12 items query the frequency, duration, and severity of mild, moderate, and severe temper outbursts and irritable mood between outbursts, as well as functional impairment in the home, school, and peer settings.

##### Clinical global impression (CGI)

The CGI is a clinician-administered tool used to assess the symptoms of mental health disorders [27]. This tool provides a scoring of initial severity on the CGI-Severity Scale (CGI-S) from 1 to 7; subsequent improvements over time during treatment are rated using the CGI-I.

Scoring for the CGI-S is as follows: 1 = normal, not ill at all; 2 = borderline ill; 3 = mildly ill; 4 = moderately ill; 5 = markedly ill; 6 = severely ill; and 7 = among the most extremely ill patients. At subsequent study visits, clinicians use the CGI-I 7-point scale to rate the patients’ total improvement based on comparison with their baseline assessment from 1 = very much improved to 7 = very much worse.

##### Child behavior checklist (CBCL)

The CBCL is a standardized form that parents complete to describe their children’s behavioural and emotional problems [32, 38]. We will use the problem items for ages 4 to 18 years that can be completed in approximately 10 min. The data obtained with the CBCL are summarized on a profile that displays the parents’ ratings of each item. The profile also displays the child’s standing on syndromes of problems that were derived from statistical analyses of CBCLs in large numbers of clinically referred children. In order to capture changes, the CBCL is completed for the preceding month (instead of 6 months).

##### Parenting and familial adjustment scales (PAFAS)

The PAFAS [28] is a 36-item questionnaire designed to assess changes in parenting practices and parental adjustment in the evaluation of individual or group parenting interventions. The inventory consists of the parenting scale with two subscales measuring parenting practices and parent–child relationships and of the Family adjustment scale measuring parental emotional adjustment and partner support. A French version has been used in a study of ADHD and irritability [39].

##### Personality assessments (HiPIC and ICU)

To measure childhood personality, we include the Hierarchical Personality Inventory for Children (HiPIC) [33], an age-appropriate version of the Five-Factor Model (FFM) of personality. The HiPIC comprises of 144 items rated on 5-point Likert scales, assessing 18 facets hierarchically organized under five higher-order dimensions that are conceptually and empirically related to the adult FFM-domains: Emotional Stability (comprising the facets Anxiety and Self-confidence), Extraversion (Shyness, Optimism, Expressiveness, and Energy), Conscientiousness (Achievement Motivation, Concentration, Perseverance, and Orderliness), Benevolence (Egocentrism, Irritability, Compliance, Dominance, and Altruism), and Imagination (including Creativity, Curiosity, and Intellect).

The ICU [35] by parent report is a 24-item questionnaire evaluating callous and unemotional traits in children and adolescents, which is reported to change with parental programs and predict quality of treatment response. Respondents are asked to rate their agreement with the different items on a 4-point Likert Scale. The total score will be used in this study.

##### Cranky thermometers

The cranky thermometers are visual analogue scales measuring irritability in youth. The first scale, Cranky Now, measures current irritability, and the second, Cranky Two Weeks, measures peak irritability within the last two weeks. Positive associations have been found between cranky thermometers and irritability scores (as determined by Kiddie Schedule for Affective Disorders and Schizophrenia) and Affective Reactivity Index scores. Results suggest that the cranky thermometers are rapidly administered, have promising psychometric properties, and demonstrate utility in measuring irritability in clinical and community settings [31].

### Other assessments

#### Five-minute speech sample (FMSS)

Expressed emotion (EE) refers to the extent to which family members express critical/hostile and emotionally over-involved attitudes and remarks toward a specific person. It has been shown to be a predictor of patient relapse in those suffering from a range of mental disorders [40]. The 5-min speech sample requires a parent to speak for 5 min, without interruption, about their relationship and attitude toward the child. The underlying notion is that what the family member says and how he or she speaks about the target person will reveal the amount of expressed emotion typically present in the household. A coding system was developed to score facets of emotional expression such as criticism and emotional over-involvement [41].

##### {18b}

A subject may withdraw from the study at any time at their own request or at the discretion of the investigator for safety, behavioural, or administrative reasons. In the event that an included subject is withdrawn, the investigator should make every effort to perform a final study visit and complete the assessments and procedures outlined in the Table 1 for the follow-up visit.

**Table 1 Tab1:** Participant timeline {13}

Visit	V0 Pre-inclusion	V1 Inclusion and randomisation	Program (NVT or PMT)	V2 M1	V3 M3 Follow-up
Day	D-90 to D0	D0	D1–D2	D30 ($$\pm 15)$$ = 1st booster session	V2 + 60 ($$\pm 15)$$ days = 2nd booster session
Protocol explanation	X				
Informed consent form		X*			
Inclusion/exclusion criteria		X*			
Demographic data		X			
Medication status		X		X	X
Parent ratings and assessments					
ARI-parent		X*		X*	X*
CBCL		X*		X*	X*
PAFAS		X*		X*	X*
HiPIC		X*			
5-minute speech sample (FMSS)		X*			X*
K-SADS	X				
ICU		X*			X*
Child ratings and assessments					
K-SADS	X				
Cranky thermometers		X*		X*	X*
Clinician ratings					
ARI – clinician		X*		X*	X*
CGI-I				X*	X*
CGI-S		X*			
Presence at sessions				X*	

Time and events of RESIST RCT for the assessment of primary and secondary endpoints; V0 = pre- inclusion visit; V1 = inclusion visit; V2 = booster session at 1 month (1 M); V3 = booster session at 3 months (3 M); D = day(s).

##### Data management {19}

Source documents are original documents and patient records from which patient data are reported in the e-CRF. The investigator must commit to allow direct access to data sources in the study during inspections, audits or inspections. For each participant there is an e-CRF, developed from the software Ennov Clinical to control data quality at entry. This software complies with the FDA recommendations on computerized systems for managing clinical trials ("Guidance for Computerized systems Used in Clinical Trials"), electronic signature ("21CFR part 11") and other domestic and international norms (CDISC, ICH, BPC 2001/20/CE…). The connection is via a username and password unique to each specific user and giving access only to the data of the centre’s user.

An audit trail function is included allowing a supervision and traceability of all actions from all users. The encrypted data is transmitted to the data-management centre via a secure internet connection. The e-CRF will be designed to capture all relevant medical information from patients included in the project.

The investigator must allow direct access to data sources in the study during inspections and audits.

The data manager will perform additional computerized consistency tests to detect the presence of non-standard, missing, aberrant, or incoherent data. These tests will be executed regularly during the participants’ recruitment and monitoring. Each identified incoherence will be the subject of a request for clarification by the researcher.

### Pseudonymization of data

In order to preserve anonymity, participants will be identified on the e-CRF by a unique identification number, the first letter of their first name, the first letter of their last name, their gender and their year of birth. A list of names of participants will be kept in the investigator's file. The investigating team will ensure that the anonymity of each participant in the study is guaranteed. The information will be collected for each participant in accordance with the study data collection form by the investigator(s) or the clinical study technician(s) in charge of the study.

### Data processing

Individual data needed for the study analysis must:be entered in the e-CRF and the non e-CRF as they are obtained, for both clinical and paraclinical data.be anonymized by the investigator.be authentified by an electronic signature of the investigator.all be entered, and missing data must be justified.

Data entered in the e-CRF are verified and validated by the Clinical Research Associate from source documents.

The Data Manager performs additional computerized tests to ensure completeness, consistency and reliability of data during the recruitment and follow-up of patients. All consistency tests are defined by the data manager in a validation test book and are approved by the investigator, the statistician, and the clinical research associate, before programming.

Each identified inconsistency will be included in the data clarification/resolution forms by the data-manager, posted online. The investigator receives an email informing him that requests for corrections are posted on the website of data entry. The investigator and / or clinical research associate connects to the website and confirms or corrects inconsistencies.

### Data coding

Data coding is integrated into e-CRF. Drugs are coded when entered using their international name (based on the WHO database). Some data are recoded by the study biostatistician before analysis.

### Data storage

Data will be saved by the Clinical Research and Epidemiology Unit (CREU) of Montpellier Hospital. Server location: Software and database reside on OVH servers (Dedicated cloud ISO 27001).

### Datatabase lock

Once quality assurance procedures have been completed, database lock will occur according to the procedures of the clinical research and epidemiology unit of Montpellier Hospital, and a database lock certificate is edited.

### Statistical methods

#### {20a}

A statistical analysis plan (SAP) will be prepared by the sponsor. Statistical analyses will be performed with SAS® version 9.4 or higher (SAS institute, North Carolina, USA).

Data will be analysed under the responsibility of the Unit of the Clinical research of CHU Montpellier with the SAS® software (SAS Institute, Cary, NC, USA).

The statistical analysis plan (SAP), covering all the analyses to be performed on all data, will be written before database lock.

Population sets

Four analysis, sets will be defined for this study:The Enrolled Set (ES) will include all subjects who sign an Informed Consent form.The Randomized Set (RS) will include all subjects who are randomized.The Full Analysis Set (FAS) will include all subjects who are randomized and have a valid primary efficacy measurement.The Per Protocol Set (PPS) will include all subjects who are in the FAS and who do not have an important protocol deviation that could affect the evaluation of the main outcome.

The FAS will be the primary set used for analyses/summaries of the primary efficacy variable, as well as for all secondary and other efficacy variables; the robustness of the analyses/summaries on the primary and key secondary efficacy variables will be assessed using the PPS.

The ES will be used for summarizing only the relative frequency of screen failures. The ES or RS will be used to establish the flow chart.

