### Explanation for the choice of comparators {6b}

In this trial, two presumably active groups are compared, the PMT group and the NVR group, against TAU. Parents in the TAU group will be offered to participate in PMT or NVR training in their respective inclusion centre after completion of the last study assessment.

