### Outcomes {12}

#### Primary endpoint

Change from baseline at 3 months of the Clinician-rated Affective Reactivity Index total score (CL-ARI) [26].

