#### Secondary endpoints

Secondary efficacy endpoint at completion:Change from baseline to follow-up at 1 month of the program of the CL-ARI [26].

Secondary efficacy endpoints at 1 month and at 3 months follow-up:Change from baseline of the Clinical Global Impression Improvement (CGI-I) scale [27].Change from baseline in the Parenting and Familial Adjustment Scale (PAFAS) [28].Change from baseline of Parent-rated ARI (P-ARI) [29, 30] and Child-rated Cranky thermometers [31].

Exploratory efficacy endpoints and putative moderators and mediators:Initial score and change from baseline of specific Child Behavior Checklist (CBCL 6–18) (parent-rated) [32]: CBCL-internalizing, externalizing, and DP/Dysregulation short scale at 1 month (M1) and at 3 months (M3).Initial score of the personality dimensions assessed by parents (Hierarchical Personality Inventory for Children; HiPIC) [33]).Initial score and change from baseline of the parental expressed emotions and reflexivity rated with the Five-minute Speech Sample (FMSS) [34] at M3.Initial score and change from baseline in the Inventory of Callous Unemotional traits (ICU) [35].

Secondary acceptability endpoints:Observance.Acceptability (questionnaire for all parents and qualitative interview in a subsample of the ancillary RESIST-QUAL; the qualitative interview will be carried out after completion of the treatment).Discontinuation from the trial due to any cause and due to specific causes.

Other assessments:Socio-demographic and early development questionnaire.Medical history.Concomitant medications.K-SADS.Clinical Global Impression Severity (CGI-S) scale at baseline.

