### Efficacy analyses

#### Primary endpoint

The full analysis set will be used for the primary endpoint.

The primary endpoint is the change from baseline (inclusion visit) at end of treatment (last visit) in the Clinician ARI total score. An analysis of variance will be performed to study the evolution of Clinician ARI total score (dependent variable) according to the three treatment groups and baseline value of ARI as a covariate. Each experimental group will be compared to the control group.

The treatment effect will be estimated by the least square mean (LSMean) of the difference with its two-sided 95% confidence interval. A graphical display of the LSMean and associated 95% confidence intervals for each treatment will be presented. In the event that marked deviations from the assumption of normality are observed, an additional analysis on the primary efficacy variable will be performed using non-parametric method.

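### The primary test leaves out randomised families without a 3-month CL-ARI, about 15% on the plan's own figure, and imputation brings them back only in a conditional sensitivity analysis

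*Protocol article*

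**What the plan says.** Statistical methods {20a} of the protocol article sets the primary population: "The Full Analysis Set (FAS) will include all subjects who are randomized and have a valid primary efficacy measurement". The primary endpoint paragraph under Efficacy analyses confirms it: "The full analysis set will be used for the primary endpoint". The model there has three groups and baseline ARI as a covariate. It has no visit term and no imputation.

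A Randomized Set is also defined, but its only stated use is descriptive: "The ES or RS will be used to establish the flow chart". For robustness, {20a} says "the robustness of the analyses/summaries on the primary and key secondary efficacy variables will be assessed using the PPS". The per-protocol set is drawn from within the FAS.

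The endpoint is worded in two ways. Outcomes {12} has "Change from baseline at 3 months of the Clinician-rated Affective Reactivity Index total score (CL-ARI". The analysis section has "The primary endpoint is the change from baseline (inclusion visit) at end of treatment (last visit) in the Clinician ARI total score".

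CL-ARI is also rated at 1 month in all arms (Follow-up assessments; Table 1), but it is used only as a separate secondary endpoint: "Change from baseline to follow-up at 1 month of the program of the CL-ARI".

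Two provisions bear on missing outcomes. Section {18b} asks investigators to try to obtain a final visit from withdrawn subjects. Section {20c} plans multiple imputation with five imputations as a sensitivity analysis, if missingness is classed as MAR or MCAR.

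**The concern.** Entry to the primary set depends on something that happens after randomisation: whether the 3-month rating was obtained. Dropping families on that basis gives up the protection of randomisation. If the families lost differ in prognosis, and differ by arm, the contrast with TAU is no longer a fair comparison of the groups as randomised.

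Loss that differs by arm is plausible here. Families know their allocation, and the arms have different reasons to stay. Of the control arm, {6b} says "Parents in the TAU group will be offered to participate in PMT or NVR training", and this offer takes effect only after the last assessment. The active arms receive all ten sessions over two days at the start, with boosters at 1 and 3 months.

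What is at stake is the estimate on which the superiority claim rests. The 1-month CL-ARI carries information on families lost after that visit, and the primary analysis ignores it.

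**Working it through.** **1. The plan's own figures.** From Sample size {14}: expected changes −2, −2 and −0.5, variance of means 0.5, SD 3, two-sided alpha 0.05, power 90%. The noncentrality is λ = 3n × 0.5 / 9. Noncentral F power is 0.8962 at n = 76 and 0.9003 at n = 77, so the stated 77 per group reproduces. For dropout, 77 / 0.85 = 90.6, and the stated 90 gives 90 × 0.85 = 76.5 analysable per group. The sample size thus already treats lost families as not analysed.

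**2. Number outside the primary test.** 0.15 × 270 = 40.5, so about 40 families. This is an expectation. Each final visit obtained under {18b} reduces it.

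**3. Do the planned safeguards bring them back?**
- Per-protocol set: a subset of the FAS, so no.
- Multiple imputation in {20c}: yes, but only as a sensitivity analysis. It depends on relating missingness status to covariates. That can give evidence against MCAR, but it cannot exclude dependence on the unseen 3-month score.

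**4. Possible size of bias (assumptions, not document figures).** Changes at M1 and M3 are taken as bivariate normal with mean −2 (active) or −0.5 (TAU) at both visits, and SD 3. Their correlation is 0.5 or 0.7. Loss is 15% in every arm. Where loss is informative, its log-odds rise with a poorer M1 change by 0.5 or 1.0 per SD (odds ratios exp(0.5) = 1.65 and exp(1.0) = 2.72). Elsewhere it is random. Every lost family has an M1 score. Means are compared without baseline adjustment. The true difference is 1.5.

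| Where loss is informative | Observed M3 only | Using M1 as well |
|---|---|---|
| Active arms only | 1.61–1.77 | about 1.50 |
| All arms alike | about 1.50 | about 1.50 |
| TAU only | 1.22–1.39 | about 1.50 |

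In the first row the four cells are 1.608 and 1.709 (correlation 0.5; slopes 0.5 and 1.0), then 1.651 and 1.773 (correlation 0.7). Relative to 1.5, that row is 7% to 18% too large (1.61/1.5 = 1.07; 1.77/1.5 = 1.18). The third row is 7% to 19% too small (1.39/1.5 = 0.93; 1.22/1.5 = 0.81).

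**5. Limit of the M1 score.** If loss is informative in the active arms only and half of the lost families leave before M1, the M1-based estimate is 1.55–1.63. That is closer to 1.5 than the observed-only figure, but not fully corrected.

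**The case against.** Several points count against a stronger charge.

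- *A reader might infer that the plan has no way to bring missing families back.* It has one: the imputation in {20c}. If its model included the M1 score, it would address the mechanism simulated above. What remains is that it is secondary and conditional, and the headline estimate does not change.
- *A reader might call this a completers' analysis.* That goes too far. Entry turns on having the outcome, not on finishing the programme. Under {18b}, withdrawn families are still sought for a final visit and can be in the FAS.
- *A reader might infer that the test will favour the active arms.* The documents do not show this. Active families also have something to return for: Table 1 places the second booster at the 3-month visit. Only an overall dropout rate is given, and the simulation shows bias in either direction or none.
- The words (last visit) in the analysis section could mean the last available visit, in which case an M1 rating might qualify a family. The 3-month reading is likelier: {12} and the objectives fix that time point, and the 77-to-90 inflation fits it. The two wordings still conflict.
- The simulation favours the M1-based estimate, because loss depends only on M1.

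The SAP is not shown and may add detail. But the choice of primary set and model is stated in the protocol, so the point does not rest on missing detail.

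**Conclusion.** The point holds in a limited form. As written, the primary test excludes randomised families without a valid 3-month CL-ARI, expected to be about 15%, or some 40 of 270. The only planned analysis that would restore them is a sensitivity analysis conditional on a judgement that observed data cannot settle.

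Neither the sign nor the size of any bias can be derived from the documents. Under the stated assumptions, a true difference of 1.5 would appear as anything from 1.22 to 1.77, and as about 1.50 if loss works alike in all arms. The plan should be changed because a better analysis of data already being collected is available at little cost. The documents do not show that the planned result would be wrong.

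**What to change.** - Make the Randomized Set the primary analysis set.
- Analyse CL-ARI change at M1 and M3 with a repeated-measures likelihood model (arm × visit, baseline × visit, unstructured covariance), taking the M3 contrasts of each active arm with TAU as primary. A smaller change would be to make the planned multiple imputation primary, with the M1 score in the imputation model.
- Bring in families with no post-baseline rating by imputation, since M1 cannot help them.
- Keep the observed-case baseline-adjusted analysis as a sensitivity analysis, and add a reference-based or tipping-point MNAR check.
- Reconcile the last-visit wording in the analysis section with the 3-month endpoint in {12}.

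The cost is revised analysis wording and a few lines of SAS PROC MIXED or imputation code. No new data or visits are needed. It should be settled before database lock, by when {20a} says the SAP will be written. The new primary analysis relies on MAR given baseline and M1. That is weaker than what the observed-case analysis needs, but it remains untestable, which is why the MNAR check belongs beside it.

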### Exploratory analyses {20b}

#### Observance

The number of performed sessions will be described. The discontinuation from the trial due to any cause (or due to specific causes) will be also reported and compared between groups.

Analyses for additional subgroups are not planned in the main study.

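### Secondary efficacy analyses are restricted to families with a primary (3-month CL-ARI) measurement, which leaves out month-1 outcomes and 3-month parent and child ratings already collected

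*Protocol article*

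**What the plan says.** Statistical methods {20a} of the protocol article sets out four populations. The FAS is "all subjects who are randomized and have a valid primary efficacy measurement". It is the primary set for the primary efficacy variable "as well as for all secondary and other efficacy variables". The per-protocol set (PPS), used to check robustness, is drawn from within the FAS. The Enrolled and Randomized Sets serve screen failures and the flow chart.

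Outcomes {12} gives the primary endpoint as the CL-ARI change at 3 months. The Efficacy analyses section words it differently: "The primary endpoint is the change from baseline (inclusion visit) at end of treatment (last visit) in the Clinician ARI total score". In Table 1 the last scheduled visit is V3, at month 3.

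The secondary efficacy endpoints include "Change from baseline to follow-up at 1 month of the program of the CL-ARI". Under the label "Secondary efficacy endpoints at 1 month and at 3 months follow-up" they add CGI-I, PAFAS, the parent-rated ARI and the child's Cranky thermometers. Table 1 and the follow-up schedule list the parent and child instruments separately from the clinician's ratings. Section {20c} plans multiple imputation as a sensitivity analysis, provided the missingness is judged MAR or MCAR.

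**The concern.** Membership of the FAS depends on one measurement, yet it governs analyses of other measurements taken earlier or from other informants. Under the natural reading, two kinds of family have usable data and are still left out of the main secondary analyses:

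- those assessed at month 1 who have no CL-ARI at month 3;
- those whose 3-month parent or child ratings were returned but whose CL-ARI is missing.

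Two of the trial's secondary objectives, irritability at other time points and irritability by other informants, rest on exactly these data. Some precision is lost. More important in principle, the month-1 comparison is made among families selected by something that happens after month 1. If staying in the trial is related to response, and differently so by arm, that comparison no longer has the full protection of randomisation.

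**Working it through.** **Step 1. Which families the rule removes.**

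| Family | Data in hand | In the FAS if the 3-month CL-ARI is required? | In the FAS if the last available CL-ARI counts? |
|---|---|---|---|
| Seen at month 1, not at month 3 | Month-1 CL-ARI, CGI-I, P-ARI, PAFAS, thermometers | No | Yes |
| Month-1 CL-ARI done; 3-month ratings returned, 3-month CL-ARI missing | All month-1 data; 3-month P-ARI, PAFAS, thermometers | No | Yes |
| Parent or child ratings only, no post-baseline CL-ARI | Those ratings | No | No |

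The first reading follows from Outcomes {12} and from Table 1, where V3 is the last visit. The second is possible under the last-visit wording of the Efficacy analyses section.

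**Step 2. The plan's own sample size.** Inputs from Sample size {14}: changes of -2, -2 and -0.5, SD 3, two-sided alpha 0.05, power 90%, dropout about 15%, 270 randomised.

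- Variance of means: the mean is -1.5, so V = (0.25 + 0.25 + 1)/3 = 0.5, as stated.
- Noncentrality at 77 per group: 3 x 77 x 0.5 / 9 = 12.83. One-way ANOVA power is 0.9003, and 77 is the smallest group size reaching 90%.
- 77/0.85 = 90.6, so 91 per group or 273 in all, against 270 stated. The difference is immaterial here.

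The sample size is not in dispute. It supplies the counts for Step 3.

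**Step 3. Families affected at month 1, with the 3-month CL-ARI required.**

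- Families without the measurement at planned dropout: 270 x 0.15 = 40.5.
- Expected FAS: 270 x 0.85 = 229.5, or 76.5 per group.
- The share of the 40.5 who attend month 1 is not in the document. Assume 25%, 50% or 75%, and call the resulting number k.
- Standard-error ratio, FAS against all families measured at month 1: sqrt((229.5 + k)/229.5).
- Pairwise power is illustrative only. It borrows the primary endpoint's difference of 1.5 and SD of 3; the FAS gives 87.1%.

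| Share attending month 1 | k left out | Available at month 1 | SE ratio | Pairwise power, all available |
|---|---|---|---|---|
| 25% | 10.1 | 239.6 | 1.022 | 88.5% |
| 50% | 20.3 | 249.8 | 1.043 | 89.7% |
| 75% | 30.4 | 259.9 | 1.064 | 90.8% |

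**Step 4. Three-month parent and child ratings.** The document gives no basis for counting families who return these but miss the CL-ARI, so no figure is offered.

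**Step 5. Whether another planned analysis restores these families.** The PPS cannot, being a subset of the FAS. Multiple imputation in {20c} depends on a judgement about the missingness mechanism, is a sensitivity analysis, and does not change the set for the main analysis.

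**The case against.** **The time point is inferred.** The FAS definition names none. If the last-visit wording means each family's last available CL-ARI, anyone with a month-1 CL-ARI stays in, and the counts in Step 3 no longer apply. This stands as a real ambiguity. It narrows the problem to families with no post-baseline CL-ARI but does not remove it.

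**Some dropouts may have a final score.** Section {18b} asks investigators to attempt a closing visit with the follow-up assessments for withdrawn subjects. So 40 is a planning figure for total dropout and may exceed the number who lack the score.

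**The plan is not without remedy.** The FAS is called the primary set, not the only one, and the imputation in {20c} extends to variables of interest generally. A reader might infer that the data are lost to every analysis. That goes too far: they are left out of the main secondary analyses and of the PPS check.

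**One definition drives both.** Redefining the FAS for the primary endpoint would change the secondary sets too, because they share it. This is correct, and the point should be settled together with any change to that definition.

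**Discontinuation and observance.** A reader might infer that the FAS also removes leavers from these. It does not. Outcomes {12} lists them as acceptability endpoints, while the FAS is assigned to efficacy variables. The article also says: "The discontinuation from the trial due to any cause (or due to specific causes) will be also reported and compared between groups". Not naming a set for them is something an article may leave to the SAP.

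**Available-case analysis is still conditional.** Using everyone measured at a visit still conditions on attending that visit. True, but it no longer conditions on a later visit or on a different instrument.

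**Conclusion.** The point holds as a modest one. The stated rule leaves observed secondary outcomes out of their main analysis for no gain. With the 3-month CL-ARI required, 15% dropout and 25% to 75% of those families attending month 1, about 10 to 30 families are left out and standard errors are about 2% to 6% wider than needed. Only the dropout rate comes from the document; the attendance share is assumed. Under the last-available reading, only families with no post-baseline CL-ARI are affected, and their number is unknown.

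A reader might go further and infer that the FAS exaggerates the month-1 effect. Suppose the planned 3-month changes already apply at month 1, lost active-arm families change by only -0.5, and lost TAU families match those who stay. With m lost families per arm of 3.4, 6.75 or 10.1, the active mean is (-2 x 76.5 - 0.5 x m)/(76.5 + m). The contrast with TAU is then -1.44, -1.38 or -1.32, against -1.50 in the FAS, an overstatement of 4%, 9% or 13%. The arithmetic is right, but the document supports none of the three assumptions. If lost TAU families also did 1.5 units worse than retained ones, both arms would shift equally and the bias would vanish; beyond that it reverses. Selection bias is therefore possible, with direction and size unsettled.

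**What to change.** In Statistical methods {20a}, apply the requirement for a valid primary measurement to the primary endpoint only, and state which visit's CL-ARI it refers to, so that Outcomes {12} and the Efficacy analyses section agree. For each secondary efficacy variable, at each visit, analyse all randomised families with that variable measured at that visit, and with a baseline value where the scale has one (CGI-I has none), in the arm to which they were allocated. Carry the same wording into the SAP.

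The cost is a wording change before database lock, with no new data collection. The number analysed will differ between endpoints and visits, so each table must show it.
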